### Sample Size

We used the G*Power 3 software (Psychonomic Society Inc) to determine the minimum sample size required for obtaining a significant medium effect size (an effect size of 0.25), given α=.05 and a statistical power of 0.80 (β=.20), using the results presented in Bonifacino et al [37]. In Bonifacino et al’s study [37], the dependent variable was assessed in 4 different stages, with 3 of them involving the total sample. Also, between the second and third assessments, the control group received the intervention. Because of this, we considered the observed differences between the first and second assessments in order to compute our sample size (postintervention difference in prevalence of 57% for the control group and 13% for the intervention group). The resulting sample size estimate was 23 per group; however, in order to ensure a sufficient effect size and taking attrition into consideration, a sample size of 55 infants per group will be used.

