### Outcomes

#### Primary Outcome Measure

The primary outcome is sustained social withdrawal assessed using the Alarm Distress Baby Scale. The Alarm Distress Baby Scale categorizes the level of sustained social withdrawal according to the sum of the score—scores from 0 to 4 indicate no sustained social withdrawal, scores from 5 to 9 indicate moderate sustained social withdrawal, and scores equal to or higher than 10 indicate severe sustained social withdrawal. Infants born moderately or late preterm will be assessed with the Alarm Distress Baby Scale during medical checkups at 2, 6, and 12 months of age.

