### Statistical Analysis

Two-tailed paired *t* tests will be used to compare covariates and dependent variables from the infant groups. A one-way analysis of covariance will be used to determine the effects of covariates (sociodemographic and neonatal intensive care unit hospitalization variables, postpartum depression, and posttraumatic stress) on the comparisons between groups (control and intervention) and between times (2, 6, and 12 months of corrected age medical checkups) regarding the dependent variable (sustained social withdrawal). Other statistical techniques such as matching, odds ratios, and logistic regression will also be used.

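### The one-way ANCOVA named for comparing both arms and the 2, 6 and 12 month visits cannot validly make those comparisons, because the same infants are scored at every visit

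*Protocol article*

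**What the plan says.** Under Primary Outcome Measure, the protocol article states that infants "will be assessed with the Alarm Distress Baby Scale during medical checkups at 2, 6, and 12 months of age". Each infant therefore contributes up to three scores on the same scale.

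Under Statistical Analysis, the method is introduced with "A one-way analysis of covariance will be used to determine the effects of covariates". The sentence goes on to apply it to comparisons between control and intervention "and between times (2, 6, and 12 months of corrected age medical checkups) regarding the dependent variable (sustained social withdrawal"). One model, called one-way, is thus given two factors, and the second is repeated within infants.

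The section names two other kinds of method. It opens with "Two-tailed paired *t* tests will be used to compare covariates and dependent variables from the infant groups", and it closes with a short list that includes logistic regression and odds ratios. No repeated-measures analysis, mixed model, GEE or infant effect is named. The article does not say whether the three visits are pooled in one model or analysed one at a time, and it gives no within-infant correlation.

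Under Study Limitations, twins are said to be randomized together to the same arm.

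**The concern.** A one-way ANCOVA compares the levels of one factor between independent subjects, adjusted for covariates. Arm fits that description. Visit does not, because its levels are measured in the same infants. The model also has no arm-by-visit term. That term matters here: guidance is given only once withdrawal has been detected at a checkup, the first being at 2 months, so an effect of the intervention should show mainly at the later visits.

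This is more than detail left to a fuller document. The article names a specific method and a specific task for it, and the two do not fit. The comparison concerned is that of the primary outcome. If the model were fitted to all scores as though they were independent, the arm comparison would be too liberal and the comparisons over time too strict. If it were fitted visit by visit, there would be no comparison over time and no stated rule for which of three results decides.

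**Working it through.** **The plan's own figure.** The article gives no type I error for this analysis. Its only reproducible design figure is in Sample Size: "The resulting sample size estimate was 23 per group", from a "postintervention difference in prevalence of 57% for the control group and 13% for the intervention group", with α = 0.05 and power 0.80. Sidedness is not stated there; two-sided is assumed.

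- Two proportions: n = [1.96·√(2·0.35·0.65) + 0.84·√(0.57·0.43 + 0.13·0.87)]² / 0.44² ≈ 17.2, so 18 per group, or 22 with continuity correction.
- Fisher's exact test has power 0.826 at 22 and 0.850 at 23 per group.

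The stated 23 is therefore close to a single comparison of two proportions. A one-way ANOVA with an effect size f of 0.25 would need 128 in total (64 per group), so that route does not give 23. The sample size calculation therefore does not settle how the three visits are to be analysed.

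**Inputs for the check.** From the article: 55 infants per arm, three visits, so up to 110 × 3 = 330 scores. Assumed: nominal two-sided 5%, equal correlation ρ between any two visits of an infant, normally distributed scores, complete data, no covariates, unrelated infants.

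**Reading A: the scores are pooled as independent.**

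- Arm test. The variance of the arm contrast is understated by the factor 1 + 2ρ, so the actual error is 2·[1 − Φ(1.96/√(1 + 2ρ))].
- Visit and arm-by-visit tests. The numerator variance is about (1 − ρ) times what the model supposes. With two numerator degrees of freedom and a large sample, the actual error is about 0.05^(1/(1 − ρ)). This is 0.05^(1/0.7) ≈ 0.014 at ρ = 0.3 and 0.05² = 0.0025 at ρ = 0.5.

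Simulation with 20,000 null trials per value of ρ agrees:

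| ρ | 1 + 2ρ | 1.96/√(1 + 2ρ) | Arm test, formula | Arm test, simulated | Visit test, simulated | Arm-by-visit test, simulated |
|---|---|---|---|---|---|---|
| 0 | 1.0 | 1.96 | 0.050 | 0.050 | 0.050 | 0.049 |
| 0.1 | 1.2 | 1.79 | 0.074 | 0.074 | 0.038 | 0.037 |
| 0.3 | 1.6 | 1.55 | 0.121 | 0.120 | 0.015 | 0.014 |
| 0.5 | 2.0 | 1.39 | 0.166 | 0.167 | 0.003 | 0.003 |
| 0.7 | 2.4 | 1.27 | 0.206 | 0.204 | below 0.001 | below 0.001 |
| 0.8 | 2.6 | 1.22 | 0.224 | 0.225 | below 0.001 | below 0.001 |

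The arm-by-visit column assumes that such a term is added to the naive model.

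**Reading B: a separate ANCOVA at each visit.** Each test holds about 0.05 at every ρ. The chance of at least one false positive among three is 1 − 0.95³ = 0.143 if visits were independent. Simulated, it is 0.140 at ρ = 0, 0.130 at ρ = 0.5 and 0.097 at ρ = 0.8. No comparison between visits is made.

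**Check on the cause.** With one value per infant (the mean of the three scores), the arm test returns to 0.047 to 0.052 for ρ from 0 to 0.8. The inflation under Reading A therefore comes from ignoring the repeated visits.

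**The case against.** The strongest reply is that the article never says the scores will be pooled or treated as independent. A one-way ANCOVA with arm as its only factor, run at each visit, is an available reading, and within-infant correlation then inflates no single test. This stands, and it is why the inflation can only be stated conditionally. It does not rescue the sentence, which also assigns the comparison between visits to the same model. Visit-by-visit fits cannot supply that comparison.

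A second reply is that the ANCOVA's stated purpose is to examine covariates, that the group comparison is given first to t tests, and that logistic regression is also listed. It is fair that the article does not call the ANCOVA the sole or confirmatory test of efficacy. But none of the other methods handles the repeated visits as described. The t tests are called paired while being assigned to two independently randomized groups, which is a separate problem and no remedy here.

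A third reply is that the stated objective is a comparison of groups and specifies no interaction. That also stands. A single named arm contrast would serve the objective. The arm-by-visit term is needed so that such a contrast can be taken at a chosen visit from one model.

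A reader might go further and infer that the plan counts every infant three times and so roughly triples the type I error. The documents do not support this. Pooling is not stated, no correlation is given, and exact tripling to 0.15 needs a correlation of about 0.43. Over correlations of 0.1 to 0.8 the factor runs from about 1.5 to 4.5. Nor can a figure be put on the further effect of twins, since the article gives neither the share of twins nor the correlation between them.

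**Conclusion.** The method is wrong as written. The one-way ANCOVA cannot validly compare both arms and repeated visits of the same infants, and no other method in the section does so. This conclusion rests on the text alone and needs no assumption.

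The size is conditional:

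- Pooled as independent: the arm test has an actual two-sided error of about 0.12 to 0.21 for an assumed correlation of 0.3 to 0.7. The visit and arm-by-visit tests fall to about 0.015 at 0.3 and 0.003 at 0.5, with a matching loss of power.
- Visit by visit: 5% per test, no comparison between visits, and about a 0.13 chance of at least one false positive at correlation 0.5 because no visit is named as primary.

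The figures assume equal correlation, normal scores, complete data and no covariates. They leave out the clustering of twins. Which case applies cannot be told from the article.

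**What to change.** Replace the one-way ANCOVA in the Statistical Analysis section with a repeated-measures mixed model for the score, with arm, visit and arm-by-visit as fixed effects. Where the outcome is a score of 5 or higher, use a GEE logistic model with the same terms. In either case, account for the repeated visits within an infant and for twins randomized together. Name one arm contrast, for example at 12 months, as the primary test, and label the contrasts at the other visits as secondary.

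The cost is a change of analysis wording and a standard model. No new data are needed. The article reports enrollment complete and results still to be published, so the change should be made and dated before the outcome is analysed by arm.

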As shown in Figure 1, all infants will receive routine pediatric care during the medical checkups at 2, 6, and 12 months of age, but in addition, infants in the intervention group will also receive the interactive guidance intervention if the Alarm Distress Baby Scale–trained neonatologists detect sustained social withdrawal during these medical checkups. All medical checkups will be video-recorded, and the videos will be assessed by external Alarm Distress Baby Scale–trained evaluators, and at every medical checkup, parents will fill out the Edinburgh Postnatal Depression Scale, the modified Perinatal Posttraumatic Stress Disorder Questionnaire, and the Impact of Event Scale–revised.

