**Figure 2 figure2:**
[figure not shown]
Summary of the steps of the interactive guidance intervention during medical checkup.

The main objective of this intervention is to reduce sustained social withdrawal behaviors in moderately and late preterm infants by (1) detecting sustained social withdrawal behaviors during medical checkup, (2) becoming attuned with the interaction rhythm of the infant, (3) meaningfully showing parents how their infant seeks to interact by pointing out specific interactive behaviors (every interaction skill displayed by the infant), and ( 4) inviting parents to engage in the interaction.

Infants born preterm have a higher probability of developing sustained social withdrawal, and withdrawn infants show poor performance during interaction [17,49]; therefore, by facilitating parental understanding of the development of their infant, by involving them in the observation of and interaction with their infant [50], and by reinforcing every seeking interactive behavior displayed by the infant during medical checkups, we can reduce sustained social withdrawal in these infants.

In the intervention group, this interactive guidance intervention will be performed if the trained neonatologist detects sustained social withdrawal during the 2, 6, and 12-month medical checkups. The interactive guidance intervention will be performed during the 20 to 30-minute medical checkup and will not require any extra time. The interactive guidance intervention will be supplemented with a written guide for parents called Early Interaction Guidelines. The objective of this written guideline is to enhance the effect of interactive guidance intervention.

In the control group, infants will receive routine pediatric care. At the 2, 6, and 12-month medical checkups (also lasting 20 to 30 minutes), parents will be given a Development Stimulation Guide which has been adapted from Ministry of Health of Chile Guidelines for the Stimulation of Development [51,52].

If any infant in the study (in either the intervention or the control group) shows sustained social withdrawal (a score or 5 or higher on the Alarm Distress Baby Scale) at the 12-month medical checkup, they will be offered additional interventions by the researcher team.

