#### Secondary Outcome Measures

The secondary outcomes measured during neonatal intensive care unit admission are neonatal pain and daily duration of parental visits, skin-to-skin contact, and breastfeeding; and the secondary outcomes measured after medical discharge are postpartum depression symptoms and posttraumatic stress symptoms which will be assessed at the 2, 6, and 12-month medical checkups. A socioeconomic survey, a substance-use survey, and a perinatal background questionnaire will be used to obtain additional information from the parents of the infants.

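### The group comparison on sustained social withdrawal is adjusted for parental depression and posttraumatic stress, which are post-randomisation secondary outcomes

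*Protocol article*

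**What the plan says.** All references are to the protocol article.

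- **Statistical Analysis.** An analysis of covariance is to show the effect of the covariates, "sociodemographic and neonatal intensive care unit hospitalization variables, postpartum depression, and posttraumatic stress) on the comparisons between groups (control and intervention", and between visits, "regarding the dependent variable (sustained social withdrawal". The text does not say which visit's parental score enters. Two-tailed t tests, described as paired, are named before it. Matching, odds ratios and logistic regression are named after it.
- **Primary Outcome Measure.** "The primary outcome is sustained social withdrawal assessed using the Alarm Distress Baby Scale", at 2, 6 and 12 months.
- **Secondary Outcome Measures.** The parental measures are outcomes: "postpartum depression symptoms and posttraumatic stress symptoms which will be assessed at the 2, 6, and 12-month medical checkups".
- **Protocol.** The parent scales are placed at the checkups: "at every medical checkup, parents will fill out the Edinburgh Postnatal Depression Scale", together with the two posttraumatic stress questionnaires. The socioeconomic and perinatal questionnaires are taken at enrolment (Inclusion Criteria), but no parental symptom score is described there.
- **Intervention.** For infants allocated to guidance: "this interactive guidance intervention will be performed if the trained neonatologist detects sustained social withdrawal during the 2, 6, and 12-month medical checkups". It is meant to work "by facilitating parental understanding of the development of their infant, by involving them in the observation of and interaction with their infant".
- **Introduction, last paragraph, and Abstract, Objective.** The main objective is the effect of guidance against routine care on withdrawal. A second, exploratory aim is the relation of withdrawal to NICU variables, parental depression and posttraumatic stress.

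**The concern.** Randomisation makes the two groups comparable on everything fixed before allocation. It gives no such protection once the comparison is conditioned on something measured after treatment has begun. Here the covariates include two measures that the protocol itself treats as outcomes, taken at visits during or after delivery of an intervention addressed to the parents.

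If guidance eases parental symptoms and this helps the infant, adjusting for those symptoms removes that part of the benefit. If unmeasured family factors drive both parental symptoms and infant withdrawal, adjustment can also distort what is left, in either direction. The resulting figure would then not answer the main objective, and a reader of the results could not tell by how much it missed.

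**Working it through.** The plan attaches no figure to this point, so there is none to reproduce. The sample size estimate of 23 per group does not enter.

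**Step 1. Timing and role of the parental scores**

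| Visit | Can guidance already have been given? | Role in the plan |
|---|---|---|
| Enrolment or NICU stay | No | No parental symptom score described |
| 2 months | Possibly, at the same visit; order of questionnaire and guidance not stated | Secondary outcome and covariate |
| 6 months | Yes, at 2 months | Secondary outcome and covariate |
| 12 months | Yes, at 2 and 6 months | Secondary outcome and covariate |

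The 6- and 12-month scores follow the start of the intervention. The 2-month score may or may not be free of its effect. No pre-randomisation score exists in the text that the covariate list could mean instead.

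The NICU variables are also listed as secondary outcomes, but they precede any guidance, so the post-treatment objection does not reach them.

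**Step 2. What adjustment does**

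In a linear model, let *a* be the group difference in parental score and *β* the fitted within-group slope of withdrawal on parental score. Then

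unadjusted contrast − adjusted contrast = *a* × *β*.

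If *a* = 0, the difference is 0. If *a* is not 0, the contrast moves by an amount that depends on *β*. Because *β* also absorbs unmeasured common causes of parental symptoms and withdrawal, it can be too large, too small or of the wrong sign. This is why the error can go either way.

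**Step 3. Illustration (mediation sizes assumed)**

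Assume a total effect of *d* = 0.5 SD. This reads the protocol's effect size of 0.25 as Cohen's *f* for two groups, *d* = 2*f*. Take 55 per group and two-sided α = 0.05. By normal approximation, power = Φ(*d*√(55/2)/σ − 1.96), with √27.5 = 5.244 and σ = 1.

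| Share of effect through parental symptoms | Adjusted contrast | Power |
|---|---|---|
| 0% | 0.50 | Φ(2.622 − 1.96) = 0.746 |
| 10% | 0.45 | Φ(2.360 − 1.96) = 0.655 |
| 20% | 0.40 | Φ(2.098 − 1.96) = 0.555 |
| 30% | 0.35 | Φ(1.835 − 1.96) = 0.450 |
| 50% | 0.25 | Φ(1.311 − 1.96) = 0.258 |

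Adjustment also reduces residual variance. Take *a* and a true slope *b* each from 0.2 to 0.5, with no confounding, and σ = √(1 − *b*²). The share removed is *ab*/0.5, from 0.04/0.5 = 8% to 0.25/0.5 = 50%. Power at those two ends is 0.692 and 0.328.

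**The case against.** The strongest reply is that no test is labelled as the primary analysis. t tests without covariates are also named, and the covariance model's stated purpose is to examine covariates, which suits the exploratory aim. On this view the adjusted model was never meant to give the treatment effect. This stands in part: a reader might infer that the plan fixes the adjusted contrast as its primary result, and the text does not say so. But Statistical Analysis does not separate the two uses. The covariance model is the only named one that covers both groups and visits, and the t tests, being described as paired, do not fit two randomised groups as written.

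A second reply is that the mechanism described is parental understanding and interaction. Nowhere is it stated that guidance lowers depression or posttraumatic stress. This stands too. Moreover, only infants detected as withdrawn receive guidance. At the background prevalence of 11.3% to 22.1%, that is 55 × 0.113 = 6.2 to 55 × 0.221 = 12.2 infants per visit. If each treated family shifted by an assumed 0.3 SD, the arm average would shift by 0.3 × 0.113 = 0.034 to 0.3 × 0.221 = 0.066 SD. With an assumed slope of 0.3 to 0.5, only 0.010 to 0.033 SD would be removed. The total effect would be diluted in the same way, however, so the share lost need not be small.

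A third reply is that the choice of visit may be left to an analysis plan not shown. That could settle the detail. But the covariate list is stated here, and every parental score described is taken after randomisation.

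**Conclusion.** The point holds as a defect in the stated covariate list. Followed as written, the between-group comparison of sustained social withdrawal is conditioned on variables that the protocol also treats as outcomes and that, at 6 and 12 months, follow the start of a parent-directed intervention. Such a contrast does not estimate the total effect in the main objective and may be biased in either direction.

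Its size is unknown. The range in the working rests on assumed values throughout, and the loss through mediation is zero if guidance leaves parental symptoms unchanged. Two stronger readings should not be drawn:

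- **That a definite part of the effect is adjusted away.** The documents give neither an effect of guidance on parental symptoms nor a slope of withdrawal on them.
- **That the covariate list overfits a logistic model.** The list belongs to the analysis of covariance. Logistic regression is named only among other techniques, with no covariates. The expected number of withdrawn infants is also not fixed: 110 × 0.113 = 12.4 to 110 × 0.221 = 24.3 at the background prevalences, but 55 × 0.57 + 55 × 0.13 = 38.5 at the rates used for the sample size.

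**What to change.** Reword Statistical Analysis so that the two aims have separate models:

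1. **Treatment effect on sustained social withdrawal.** Use pre-randomisation covariates only: the randomisation strata (hospital, single or twin pregnancy, Kangaroo Care at Hospital San Jose), gestational age, and other birth or enrolment variables. Leave out the parental scores at all visits.
2. **Do not use the 2-month Alarm Distress Baby Scale score as a baseline.** It is one of the primary assessments. It comes from a visit at which guidance can be given and at which the two groups see different neonatologists (Blinding, Care Providers).
3. **Parental depression and posttraumatic stress.** Compare them between groups as the secondary outcomes they are.
4. **Second aim.** Use the parental scores as explanatory variables only in a separate association model, labelled exploratory. NICU records that may have accrued after randomisation fit there as well.

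The cost is a change of analysis wording. No new data are needed, the exploratory aim is kept, and the article describes the trial as ongoing with results unpublished.

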### Ethics

The study was approved by the *Comité Ético Científico de la Facultad de Medicina* (Scientific and Ethics Committee of the Faculty of Medicine), Universidad del Desarrollo (approval record 2017-05) on April 25, 2017. The clinical trial was registered at the United States National Institutes of Health (clinicaltrials.gov; NCT03212547) and approved on July 7, 2017. Informed oral and written consent were obtained from the accompanying parent of each infant included in the study.

